### Sample Size

#### Aim 1

In determining the sample size for qualitative studies, the key goals are to develop case-oriented perspectives, select participants with a range of characteristics and perspectives, and achieve saturation (ie, the point at which subsequent interviews fail to produce new themes) [56]. Research indicates that typically, saturation is reached with 12 to 16 interviews. As we are also obtaining qualitative data on veterans who did not adhere to the treatment (approximately 23% of the sample), we increased our recruitment target slightly to 16 to 20 veterans to allow for a sufficient sample of veterans who completed Deprexis treatment, as well as those who terminated treatment early (ie, did not complete the posttreatment or follow-up questionnaires).

#### Aim 2

Effect sizes in the general population Deprexis RCT for participants with mild to moderate depression (QIDS-SR-16 score <21) ranged from Cohen *d*=0.65 to Cohen *d*=0.90. Some evidence suggests that effect sizes for psychological interventions may be smaller for veterans [57]; therefore, we estimate that effect sizes are at least medium (Cohen *d*=0.50) for measures of functioning and large (Cohen *d*=0.80) for depressive symptoms. To achieve 0.8 power at an α of .05, a total of 102 participants need to be recruited. Accounting for 23% attrition over time, we will randomize 132 participants at baseline. In the general population trial, approximately 57% (n=213) of the randomized participants were high engagers (>90 min), and effect sizes were slightly higher in the high engager group (Cohen *d*>0.67) than in the overall sample. Thus, we expect to be adequately powered for analysis in this subgroup.

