## Methods

### Trial Design

This study is an individually randomized, parallel, 2-group therapy trial. A total of 132 veterans will be randomized in a 1:1 fashion to either a Deprexis intervention or a TAU control group.

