### Outcomes

In aim 1, qualitative veteran feedback on the Deprexis intervention and study procedures will be obtained; no quantitative analyses will be completed. Broadly, the posttreatment interview questions will cover the following content areas: (1) motivation toward, and barriers to, treatment and participation in the study; (2) Deprexis content, presentation, adherence, and usability; (3) perceptions of study procedures; and (4) changes experienced in mood, behavioral engagement, or interpersonal interactions after Deprexis treatment.

In aim 2a, we will test whether Deprexis is effective for decreasing depressive symptoms and improving functional outcomes in veterans presenting for VA health care with mild to moderate depressive symptoms. The primary outcomes for this aim are depressive symptoms (assessed with the QIDS-SR-16) and functioning (assessed with the World Health Organization Disability Assessment Schedule II [WHODAS-II] and the Sheehan Disability Scale [SDS]). The secondary outcomes are other psychopathology (assessed with the PTSD Checklist for Diagnostic and Statistical Manual of Mental Disorders, Fifth Edition [PCL-5] and the PDSQ), social functioning (assessed with the Interpersonal Support Evaluation List–Short Form [ISEL-SF] and the Inventory of Interpersonal Problems–Short Circumplex Form [IIP-SC]), and quality of life (assessed with the Quality of Life Scale [QLS]).

Exploratory analyses in aim 2b will examine whether demographic variables (sex, gender, age, race, ethnicity, and education), PTSD symptom severity (assessed with the PCL-5), comorbidity (assessed with the PDSQ), treatment credibility (assessed with the Credibility and Expectancy Questionnaire), frequency of study support, and Deprexis use moderate treatment effects.

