For aim 2, linear mixed effects regression [60] with restricted maximum likelihood estimation will be used to model continuous outcomes (eg, changes in psychosocial functioning outcomes and depressive symptoms), and logistic models will be used to model changes in dichotomous outcomes (eg, significant change: ≥50% improvement in scores) over time. Linear mixed effects regression models will initially be fit using an interactive model (eg, treatment condition+time+treatment condition×time) and compared to an additive model (eg, treatment condition+time) using a likelihood ratio test. This nested comparison serves as a significance test of the treatment×time interaction and will be reported as such in the analyses [61]. *Condition* (treatment or TAU), *time* (before treatment, after treatment, and follow-up), and their interaction will be entered as fixed effects, and *participant* will be entered as a random effect (ie, random intercepts). Cohen *d* for the treatment×time interaction will be calculated using an effect size derived from the mean pretreatment-to-posttreatment and follow-up change in the treatment condition minus the mean pretreatment-to-posttreatment and follow-up change in the TAU control divided by the pooled pretreatment SD [62]. Simulations suggested that this effect size estimate was the most stable and robust for these types of treatment designs [63]. When comparisons are made within a time period, Welch 1-tailed *t* tests will be performed because they are ideal when the 2 samples have unequal variances or unequal sample sizes [64]. When comparisons are made within a treatment condition over time (repeated measures), a paired samples *t* test will be performed. As participants can engage in nonstudy mental health treatment, nonstudy treatment use will be included as a covariate in all analyses.

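### The sample size of 102 matches a one-sided two-sample t test for functioning, while the efficacy test is a non-directional treatment×time test, so its stated 80% power is unsupported

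*Protocol article*

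**What the plan says.** Protocol article, Sample Size, Aim 2: the planning assumption is that "effect sizes are at least medium (Cohen *d*=0.50) for measures of functioning and large (Cohen *d*=0.80) for depressive symptoms". The requirement follows: "To achieve 0.8 power at an α of .05, a total of 102 participants need to be recruited". It is then inflated: "Accounting for 23% attrition over time, we will randomize 132 participants at baseline". The paragraph names no test, no sidedness and no correlation between repeated measurements. Trial Design gives 1:1 allocation.

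Outcomes: "The primary outcomes for this aim are depressive symptoms (assessed with the QIDS-SR-16) and functioning", with functioning measured by the WHODAS-II and the SDS. Two of the three primary outcomes are therefore planned at d=0.50.

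Statistical Methods: a mixed model with the treatment×time interaction is compared with one without it by a likelihood ratio test, and "This nested comparison serves as a significance test of the treatment×time interaction and will be reported as such in the analyses". Time has three levels: before treatment, after treatment and follow-up. The only mention of sidedness concerns a different set of tests: "When comparisons are made within a time period, Welch 1-tailed" t tests are used. The reason given is unequal variances or unequal sample sizes.

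**The concern.** A likelihood ratio test of an interaction has no direction, and with time as a three-level factor it has 2 degrees of freedom. If the sample size was worked out for a one-sided comparison of two means, the quoted power belongs to a different test from the one reported as the efficacy result. The outcomes affected are the two functioning measures, and the Discussion describes functional outcomes as an explicit focus of the trial. A null result on functioning would then be read against a power figure that was never established for that test.

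The one-tailed Welch comparisons add a smaller problem. At a one-tailed .05 level, the false-positive rate in the favourable direction is 5%, against 2.5% for a two-tailed test at .05. Such a test also cannot show worsening. The reason given supports Welch's form of the t test, not the choice of one tail.

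**Working it through.** **Inputs.** From the article: d=0.50 (functioning), d=0.80 (depressive symptoms), α=.05, power 0.80, 1:1 allocation, 102 analysed, 23% attrition, three time points. Assumed, because the article does not give it: a common correlation r between any two visits (compound symmetry) and equal SDs.

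**Step 1: reproduce 102.** For a two-sample t test with n per arm, the noncentrality is d√(n/2) on 2n−2 degrees of freedom. At n=51 and d=0.50 it is 0.50×√25.5=2.525.

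- One-sided .05, d=0.50: n=50 gives 79.9% and n=51 gives 80.6%. The smallest total is 102, an exact match.
- Two-sided .05, d=0.50: n=63 gives 79.5% and n=64 gives 80.1%. The total is 128, not 102.
- d=0.80: 42 one-sided or 52 two-sided. Neither matches.
- Two-sided with Bonferroni correction, d=0.50: 156 (α/2) or 172 (α/3). Neither matches.
- Attrition: 102/0.77=132.5, consistent with 132 randomized. So 102 is the number to be analysed.

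**Step 2: two-sided power at 51 per arm (two-sample t test).**

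- d=0.50: 70.6%.
- Effect detectable with 80% power: d=0.56.
- d=0.80: 97.9%.

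**Step 3: the planned interaction test.** Let δ be the between-arm differences in change from baseline at the two later visits, in baseline SD units. Under compound symmetry the two changes have covariance V=(1−r)[[2,1],[1,2]]. The 2-df test then has noncentrality

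λ=(n/2)·δ′V⁻¹δ=(n/2)·(2δ₁²−2δ₁δ₂+2δ₂²)/[3(1−r)],

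and power is the probability that a noncentral chi-square (2 df, λ) exceeds 5.991.

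- Effect sustained, δ=(0.50, 0.50): λ=25.5×0.50/[3(1−r)]=4.25/(1−r).
- Effect halved by follow-up, δ=(0.50, 0.25): λ=25.5×0.375/[3(1−r)]=3.1875/(1−r).

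| r | λ, sustained | Power, sustained | λ, halved | Power, halved |
|---|---|---|---|---|
| 0.3 | 6.07 | 59% | 4.55 | 47% |
| 0.4 | 7.08 | 66% | 5.31 | 53% |
| 0.5 | 8.50 | 75% | 6.38 | 61% |
| 0.6 | 10.63 | 84% | 7.97 | 72% |
| 0.7 | 14.17 | 93% | 10.63 | 84% |

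With the effect sustained, power reaches 80% at r of about 0.56.

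**Step 4: can a two-sided calculation also return 102?** Yes, if a correlation is supplied. The variance of a pre-to-post change is 2(1−r), and at r near 0.60 a two-sided change-score calculation gives 102. A baseline-adjusted calculation, with variance 1−r², gives about 102 at r near 0.44. Neither correlation appears in the article.

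**The case against.** Two stronger readings are tempting, and the article supports neither.

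- A reader might infer that 102 can only have come from a one-sided test. Step 4 shows otherwise: an unstated correlation near 0.60 (change score) or 0.44 (baseline-adjusted) leads to about the same number two-sided. The one-sided origin is the likeliest, because it matches to the unit on the stated inputs alone, but it remains an inference.
- A reader might infer that the interaction test has 71% power and that the trial is shown to be underpowered. The 70.6% belongs to a two-sided two-sample t test. The interaction test lies above or below 80% according to r, so a shortfall is possible but not proven.

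There is more on the plan's side. One-tailed between-arm t tests are declared in Statistical Methods and the hypothesis in Aims is directional, so 102 does agree with one planned comparison. The full protocol may state sidedness and correlation, and their absence from an article would not by itself be a fault. The d=0.50 is called a minimum, set below an earlier range of 0.65 to 0.90; at d=0.65, 51 per arm gives 90% power two-sided. The intention-to-treat analysis uses all 132 with imputation, so partial follow-up adds some information beyond 102 completers.

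These points reduce the practical consequence but leave the mismatch. The article attaches 80% power to 102 without qualification, its stated inputs yield that figure for a one-sided t test, and the test it reports as the efficacy result is a different, non-directional one.

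**Conclusion.** The concern holds as a mismatch between the sample-size claim and the planned efficacy test. It is confined to functioning (WHODAS-II and SDS at d=0.50). On a two-sided two-sample basis, 102 analysed give about 71% rather than 80%. For the interaction test, the plausible span is about 59% to 93% for r from 0.3 to 0.7 if the effect is sustained, and about 61% at r=0.5 if it halves by follow-up. These figures assume 51 analysed per arm, compound symmetry, equal SDs and time fitted as a three-level factor. Depressive symptoms at d=0.80 are not in question, with about 98% two-sided on the two-sample basis. The one-tailed Welch comparisons are a secondary matter: the article does not call them confirmatory, but the reason it gives does not justify one tail.

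**What to change.** 1. In the Aim 2 sample-size paragraph, name the test behind 102, its sidedness and any correlation assumed.
2. Report there what 102 analysed provide two-sided: about 71% for d=0.50 on a two-sample basis, 80% for d=0.56, and about 98% for d=0.80. Add the power of the treatment×time test for functioning over a range of r, with the effect both sustained and reduced at follow-up.
3. In Statistical Methods, make the within-time Welch comparisons two-tailed.

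No change in enrolment is proposed. Keeping 80% at d=0.50 on a two-sided two-sample basis would need 128 analysed, or 128/0.77=166.2, so 167 randomized. The cost of the fix is rewording, and the stated power for functioning becomes less favourable. The article reports four participants recruited at submission, so at that stage the restatement could precede nearly all outcome data.

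### The 102 participants for 0.8 power match a one-sided t test at d=0.50; the power of the planned treatment×time test for the functioning outcomes is not shown

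*Protocol article*

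**What the plan says.** The Sample Size section (Aim 2) plans on the assumption that "effect sizes are at least medium (Cohen *d*=0.50) for measures of functioning and large (Cohen *d*=0.80) for depressive symptoms". It continues: "To achieve 0.8 power at an α of .05, a total of 102 participants need to be recruited". It then adds dropout: "Accounting for 23% attrition over time, we will randomize 132 participants at baseline". Trial Design gives the allocation: "A total of 132 veterans will be randomized in a 1:1 fashion". The paragraph does not name the test, its sidedness or a within-person correlation.

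Outcomes lists three primary measures: QIDS-SR-16 for depression, and WHODAS-II and SDS for functioning.

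Statistical Methods fits a random-intercept mixed model over three time points. It compares the models with and without the treatment×time term by a likelihood ratio test, and says of this: "This nested comparison serves as a significance test of the treatment×time interaction and will be reported as such in the analyses". The same section specifies one-tailed Welch t tests for comparisons at a single time point. It defines the interaction effect size as the difference in mean change divided by the pooled pretreatment SD.

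**The concern.** A sample-size statement should give the power of the test that will decide the question. Here the total comes out exactly for a one-sided t test on a single score, whereas the treatment effect is to be tested by a likelihood ratio test that has no direction. A reader who sees α .05 without qualification will usually assume a two-sided test, and 102 does not give 0.8 power for a two-sided t test at d=0.50.

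What is at stake is how a null result is read. WHODAS-II and SDS are two of the three primary outcomes, and the Discussion stresses functional outcomes. A null finding on them would be taken as coming from a trial with 80% power at d=0.50, which the article does not establish for its main test.

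**Working it through.** **Inputs from the article.** d=0.50 (functioning), d=0.80 (depression), α=.05, power 0.8, total 102, 23% attrition and 132 randomized (Sample Size); 1:1 allocation (Trial Design); three time points and the likelihood ratio test (Statistical Methods).

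**1. Reproduce the stated total.** Two-sample t test, noncentral t with 2n−2 degrees of freedom and noncentrality d·√(n/2):

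| d | Sidedness | n per arm for 0.8 power | Total |
|---|---|---|---|
| 0.50 | one-sided | 50.15, so 51 | **102** |
| 0.50 | two-sided | 63.8, so 64 | 128 |
| 0.80 | one-sided | 21 | 42 |
| 0.80 | two-sided | 26 | 52 |

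So d=0.50 drives the size, and only the one-sided row gives 102. The normal approximation gives 100 (one-sided) and 126 (two-sided) at d=0.50. The attrition step is consistent to rounding: 132 × 0.77 = 101.6.

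**2. t-test power at 102 analysed (51 per arm).** At d=0.50 the noncentrality is 0.5 × √25.5 = 2.52.

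- One-sided, d=0.50: 0.806.
- Two-sided, d=0.50: 0.706.
- Two-sided, d=0.80: 0.979.
- Effect giving 80% two-sided power: d=0.56.

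**3. Power of the planned interaction test.** Assumptions that are not in the article: time is categorical (2 df), compound symmetry as implied by random intercepts, d on the pretreatment SD, and within-person correlation ρ. With SD set to 1, the two changes from baseline have covariance (1−ρ)·[[2, 1], [1, 2]]. With δ the vector of arm differences in change and 51 per arm, the noncentrality is

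λ = (51/2) · δ′ [[2, 1], [1, 2]]⁻¹ δ / (1−ρ).

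- Effect 0.5 at both later visits: δ′[[2, 1], [1, 2]]⁻¹δ = 0.25 × 2/3 = 0.1667, so λ = 4.25/(1−ρ).
- Effect 0.5 after treatment and 0.25 at follow-up: (0.50 − 0.25 + 0.125)/3 = 0.125, so λ = 3.19/(1−ρ).

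Power from the noncentral chi-square with 2 df at .05:

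| ρ (assumed) | Sustained effect | Effect halved at follow-up |
|---|---|---|
| 0.3 | 0.59 | 0.47 |
| 0.4 | 0.66 | 0.53 |
| 0.5 | 0.75 | 0.61 |
| 0.6 | 0.84 | 0.72 |
| 0.7 | 0.93 | 0.84 |

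With a sustained effect, 0.80 is reached at ρ of about 0.56. An F reference with 200 denominator degrees of freedom changes these values by no more than about 0.01.

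**The case against.** **The plan does contain one-tailed tests.** It specifies one-tailed Welch tests, and the Aims state a directional hypothesis, so 102 has a matching test. That stands as a probable explanation of the number. It does not carry over to the interaction test, which is the one the article designates for the treatment effect.

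**A two-sided calculation with an unstated correlation could also lie behind 102.** A two-sided change-score comparison at ρ of about 0.6, or an ANCOVA at a correlation of about 0.45, has about 0.80 power with 102. This cannot be excluded. It needs an input the article does not give, whereas the one-sided t test reproduces 102 with nothing added.

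**The correlation may be high.** The article cites a test-retest r of 0.98 for WHODAS-II and a reliability of 0.73 for SDS. These are not correlations from before to after treatment and probably overstate them, but they are a good reason not to stop the range at 0.6.

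**The assumptions may be cautious.** The article calls d=0.50 a minimum and cites effects of 0.65 to 0.90; at d=0.65 a two-sided t test with 102 has 0.90 power. The intention-to-treat analysis includes all 132, and with 132 complete observations the two-sided t test at d=0.50 has 0.81. Both points are fair, but the stated 0.8 was claimed at d=0.50 after discounting for attrition.

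**A stronger reading is tempting:** that the planned analysis has 0.71 power, or that the trial must enlarge to 128 analysed. The document does not support either. The 0.71 belongs to a two-sided t test on a single score, which is not the planned interaction test; the power of that test may lie below or above 0.8.

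**Conclusion.** The point holds as a fault in the power statement, not as proof of an underpowered trial. On the stated inputs alone, 102 is the one-sided t-test total. The article does not disclose this, and it does not match the non-directional test of the treatment effect. The gap in t-test terms is 0.81 against 0.71, or 102 against 128 analysed.

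For the interaction test, power at d=0.50 is undetermined: about 0.47 to 0.93 over assumed correlations of 0.3 to 0.7 and the two effect patterns, under compound symmetry with 102 analysed. The 0.8 is therefore not shown for WHODAS-II and SDS. On the two-sided t-test benchmark, the depression outcome at its assumed d=0.80 is not in difficulty (0.98).

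**What to change.** Keep 132 randomized and reword the Aim 2 sample-size paragraph:

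- State that 102 is the total for a one-sided .05 two-sample t test at d=0.50.
- Give the two-sided t-test benchmark with 102 analysed: about 0.71 at d=0.50, 80% at d=0.56, and 0.98 at d=0.80.
- Replace the unqualified 0.8 with the power of the treatment×time likelihood ratio test over a stated range of within-person correlations, with the assumed effect at follow-up made explicit.
- If a two-sided calculation with an assumed correlation was in fact used, name that test and that correlation instead.

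The cost is a sentence or two of text and a short calculation. No extra participants are needed, and no analysis changes. The stated power for functioning may turn out lower or higher than 0.8, depending on the correlation the investigators can justify.

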### Assignment of Intervention: Allocation and Blinding

#### Allocation Sequence Generation

Computer-generated stratified block randomization with block sizes of 4 and 8 will be performed by the research technician using a web-based application. As depression severity has previously been associated with Deprexis treatment response, randomization will be stratified by depression severity, consisting of 3 categories: mild=QIDS-SR-16 score 6-10, mild to moderate=QIDS-SR-16 score 11-15, and moderate=QIDS-SR-16 score <16-20. Stratification was limited to depression severity because minimizing the number of strata is recommended in trials that enroll relatively few participants.

#### Who Will Be Blinded?

The use of a TAU control condition precludes the blinding of participants and research staff. Confounds due to research staff not being blinded will be minimal because all assessment and intervention components will be completed remotely without research staff support. Given that we only use self-report measures, the involvement of research staff in responses will be very limited, and rater effects are unlikely.

### Data Collection, Management, and Analysis

#### Plans to Promote Participant Retention

Participants will receive SMS text and email reminders with embedded links to their Qualtrics follow-up assessments. Research technicians will attempt to make telephone contact with veterans who fail to complete follow-up assessments within the designated time frame.

#### Data Management

Various steps will be taken to ensure data quality. First, questionnaire data will be directly downloaded from Qualtrics into a Microsoft Excel file. Statistical software code will then be used to score the questionnaires. Two different research technicians will double score the questionnaires, and any discrepancies will be reviewed by the study PI. All identifying participant data will be stored behind a VA firewall to ensure data security.

#### Statistical Methods

Aim 1 preliminary analyses will be conducted using established methods for qualitative research [58]. Debriefings will occur after each interview through a structured audio review and matrix displays. The debriefing format will highlight the content and key findings from each interview, enabling the study team to determine when saturation has been reached. The findings from these debriefings will be categorized into “rapid codes” on a matrix display signifying the key areas of the interview agenda they represent (eg, barriers to treatment, Deprexis content, and changes experienced in mood and functioning). Matrix displays create a visual representation of responses to key codes from each participant by lining up each primary response to a question side by side in a single row of a spreadsheet. Rapid codes are summarized into themes, revised continually, and used to determine saturation and inform intervention content areas. Subsequently, during formal analyses, all interviews will be recorded, transcribed verbatim, deidentified, and reviewed for accuracy against the recordings. Drawing from the literature, the interview agenda will be used to develop an initial coding structure that captures participant responses. An iterative process of transcript review will generate additional codes that will be added to the coding structure. The final coding structure will then be used by the research team to code and review all transcripts for concordance. The final codes will be entered into ATLAS.ti (ATLAS.ti Scientific Software Development GmbH) [59], a qualitative data management software tool, for review using applied thematic analysis. Applied thematic analysis is a systematic approach to coding, organizing, and interpreting qualitative data to best capture meaning via themes across participants’ responses; for example, within any given code, this approach captures the breadth of responses to create an overall theme. In accordance with the purpose of aim 1—to improve the further study and uptake of Deprexis in the RCT—we will look carefully for themes that describe the intended needs and desires of veterans, the perceived utility of Deprexis, changes noted in mood and functional domains, and other emergent themes. These themes will be used to identify several potentially modifiable components of Deprexis, which can be used to guide current and future study efforts.

For aim 2, linear mixed effects regression [60] with restricted maximum likelihood estimation will be used to model continuous outcomes (eg, changes in psychosocial functioning outcomes and depressive symptoms), and logistic models will be used to model changes in dichotomous outcomes (eg, significant change: ≥50% improvement in scores) over time. Linear mixed effects regression models will initially be fit using an interactive model (eg, treatment condition+time+treatment condition×time) and compared to an additive model (eg, treatment condition+time) using a likelihood ratio test. This nested comparison serves as a significance test of the treatment×time interaction and will be reported as such in the analyses [61]. *Condition* (treatment or TAU), *time* (before treatment, after treatment, and follow-up), and their interaction will be entered as fixed effects, and *participant* will be entered as a random effect (ie, random intercepts). Cohen *d* for the treatment×time interaction will be calculated using an effect size derived from the mean pretreatment-to-posttreatment and follow-up change in the treatment condition minus the mean pretreatment-to-posttreatment and follow-up change in the TAU control divided by the pooled pretreatment SD [62]. Simulations suggested that this effect size estimate was the most stable and robust for these types of treatment designs [63]. When comparisons are made within a time period, Welch 1-tailed *t* tests will be performed because they are ideal when the 2 samples have unequal variances or unequal sample sizes [64]. When comparisons are made within a treatment condition over time (repeated measures), a paired samples *t* test will be performed. As participants can engage in nonstudy mental health treatment, nonstudy treatment use will be included as a covariate in all analyses.

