### Measures

The following primary outcomes (assessed at all time points) are administered through Qualtrics:

The QIDS-SR-16 [31] is a 16-item self-report measure of depressive symptom severity. This measure takes 5 to 7 minutes to complete and assesses the 9 Diagnostic and Statistical Manual of Mental Disorders, Fourth Edition (DSM-V), symptom criterion domains for depression (eg, “There is no change in my usual appetite”) and has been shown to be highly internally consistent (Cronbach α=0.86). The QIDS-SR-16 demonstrates concurrent validity with measures assessing similar outcomes (*r*=0.86-0.65) and is sensitive to symptom change [31]. Scores of >6 are indicative of meaningful depressive symptoms. The QIDS-SR-16 will serve as a primary eligibility criterion, specifically a QIDS-SR-16 score between 6 and 20. To verify the duration of depressive symptoms, we will include an item adapted from the Clinical Interview Schedule–Revised, which will assess the duration of depressive symptoms on a 6-point scale.

The WHODAS-II [35] is a 36-item self-report questionnaire, which takes 5 to 20 minutes to complete. The measure assesses functional disability across 7 domains: understanding and communicating, getting around, getting along with people, life activities, work, participation in society, and self-care (eg, “In the last 30 days, how much difficulty did you have in concentrating and doing something for 10 minutes?”). The WHODAS-II total score is scaled from 0 to 100, with higher scores indicating greater disability. The WHODAS-II has high test-retest reliability (*r*=0.98) and moderate to good concurrent validity with measures assessing similar outcomes (*r*=0.45-0.65), and it is sensitive to change in functional disability after treatment [35].

The SDS [36] is a 3-item self-report measure of symptom-related disability (eg, “The symptoms have disrupted your work/school life”) that has been used in previous Deprexis trials. The SDS takes approximately 5 minutes to complete, and items are summed (range 0-30), with higher scores indicating greater disability. The SDS was developed as a global measure of the impact of mental illness on work and school activities, family relationships, and social functioning. The SDS is highly internally consistent (Cronbach α=0.89) and has good reliability (*r*=0.73and high construct validity [37]; in addition, it is sensitive to treatment effects [38].

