#### Methods for Additional Analyses

In an exploratory and hypothesis-generating mode, potential moderators for Deprexis treatment effects will be examined. Generalized linear mixed models with robust maximum likelihood estimation will be used to model continuous outcomes (eg, changes in psychosocial functioning outcomes and depressive symptoms), and logistic models will be used to model changes in dichotomous outcomes (eg, significant change: ≥50% improvement in scores) over time. *Participant* will be entered as a random effect (ie, random intercepts). Each potential moderator will be examined in a separate model for changes in primary outcomes (QIDS-SR-16, WHODAS-II, and SDS). Each model will include main effects for the potential moderator and time (before treatment, after treatment, and follow-up), 2-way interactions (moderator×time and time×treatment condition), and a 3-way interaction (moderator×time×treatment condition). To prevent spurious associations, the α value will be Bonferroni corrected [65]. A variable will be considered a moderator of treament effects if there is a significant 3-way interaction (moderator×time×treatment condition) after treatment or at 8-week follow-up.

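### The treatment×time test is a likelihood ratio comparison of models said to be fitted by REML but differing in fixed effects, and no maximum-likelihood refit is stated

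*Protocol article*

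**What the plan says.** In the protocol article, Statistical Methods, the aim 2 analysis uses linear mixed effects regression "with restricted maximum likelihood estimation will be used to model continuous outcomes". An interactive model (condition, time and their product) is fitted first and is then "compared to an additive model (eg, treatment condition+time) using a likelihood ratio test". The article gives this comparison a definite role: "This nested comparison serves as a significance test of the treatment×time interaction and will be reported as such in the analyses".

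The section also says which terms are fixed and which are random. Condition and time ("before treatment, after treatment, and follow-up), and their interaction will be entered as fixed effects") form the fixed part, and a participant intercept is the only random term. The two models being compared therefore share the same random part and differ only in the interaction columns.

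Maximum likelihood appears once, under Methods for Additional Analyses, and only for the exploratory moderator models: "Generalized linear mixed models with robust maximum likelihood estimation will be used to model continuous outcomes". The primary outcomes that go through the REML models are the QIDS-SR-16, the WHODAS-II and the SDS. Their scales differ. In the Measures section, "The WHODAS-II total score is scaled from 0 to 100", while the SDS is a sum running from 0 to 30.

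**The concern.** A REML likelihood is the likelihood of the data after the fixed effects have been projected out. Two models with different fixed effects project out different things, so their REML likelihoods describe different sets of error contrasts and are not comparable. The term log|X′V⁻¹X| in each of them does not cancel in the ratio. The usual chi-square reference holds for ML likelihoods, not for these.

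The comparison is the named significance test of treatment×time for every continuous primary outcome. An analyst who follows the text literally would report p values that move with the measurement scale and with the design-matrix coding, neither of which carries any information about the treatment.

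**Working it through.** The article reports no figure for this test, so there is none to reproduce. The check has an algebraic part, which needs no assumed values, and a simulation part, which does.

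**Inputs from the article.** Three time points, two arms, 1:1 allocation, a random intercept per participant, α = 0.05, 102 evaluable participants (102/2 = 51 per arm) and 132 randomized (132/2 = 66 per arm).

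**Assumptions, because the article is silent.** Outcome SD of 4, 7 or 18 as a plausible range for scores on scales of this kind; within-person correlation 0.5; complete data; several codings of the factors.

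**1. Dependence on units.** Let n be the number of observations and p the number of fixed-effect columns. Multiplying the outcome by c multiplies the estimated variance by c², so the maximized log-likelihood changes by

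- REML: −(n − p) ln c
- ML: −n ln c

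With time as a three-level factor, p = 6 in the interactive model and p = 4 in the additive model. The statistic is twice the difference in log-likelihood, so it changes by

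- REML: −2[(n − 6) − (n − 4)] ln c = 4 ln c
- ML: −2[n − n] ln c = 0

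A covariate present in both models, such as nonstudy treatment use, adds one to each p and leaves the 4 ln c unchanged.

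**2. The same data on three scales.** One simulated dataset (66 per arm, SD 18, true difference d = 0.5 at both later visits) was referred to chi-square with 2 df, for which p = exp(−statistic/2). Each division by 10 should lower the REML statistic by 4 ln 10 = 9.21.

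| Outcome scale | REML statistic | p | ML statistic | p |
|---|---|---|---|---|
| As generated | 22.74 | 0.000012 | 14.98 | 0.00056 |
| Divided by 10 | 13.53 | 0.0012 | 14.98 | 0.00056 |
| Divided by 100 | 4.32 | 0.116 | 14.98 | 0.00056 |

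22.74 − 9.21 = 13.53 and 13.53 − 9.21 = 4.32, as the algebra requires.

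**3. Dependence on coding.** Multiplying one interaction column by k multiplies |X′V⁻¹X| of the interactive model by k² and leaves the additive model alone, so the REML statistic moves by −2 ln k. With linear time, for example, recoding visits from 0, 1, 2 to weeks 0, 8, 16 gives k = 8 for the interaction column, a shift of −2 ln 8 = −4.16 with no change in the data. (The time column is rescaled in both models, so its contribution cancels.)

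**4. Type I error.** Simulated rejection rates under the null at nominal 5%:

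| REML-based test | Per arm | SD 4 | SD 7 | SD 18 |
|---|---|---|---|---|
| Three-level time, dummy coding | 51 | 17.6% | 53.1% | 100% |
| Three-level time, dummy coding | 66 | 12.4% | 38.0% | 100% |
| Three-level time, sum-to-zero coding | 51 | 1% | 5% | 32% |
| Three-level time, sum-to-zero coding | 66 | 1% | 2% | 24% |
| Linear time 0, 1, 2 | 51 | 5% | 10% | 36% |
| Linear time in weeks 0, 8, 16 | 51 | 0.7% | 0.8% | 2% |
| Linear time in weeks 0, 8, 16 | 66 | 1% | 1% | 2% |

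The dummy-coding rows rest on 1,500 null datasets each. The 51-per-arm rows for the other codings rest on 600 per cell, where the standard error of a true 5% rate is √(0.05 × 0.95/600) = 0.9 percentage points. A separate run of the dummy-coded case at 66 per arm gave 14%, 34% and 100%. The ML-based test rejected in 5.2% (51 per arm) and 4.7% (66 per arm) of the 1,500 datasets, and in about 3% to 7% across the smaller runs.

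With dummy coding and an outcome scaled to SD 1, the REML statistic was negative in 79% (51 per arm) and 85% (66 per arm) of null datasets. A valid likelihood ratio statistic for nested models cannot be negative.

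**The case against.** The strongest defence is that the two statements can be read apart. REML is named as the estimator, the likelihood ratio test is named as the test, and the article never expressly says that restricted likelihoods go into the test. Estimating by REML and testing nested fixed effects on ML fits is ordinary practice, and some software refits by ML before such a comparison. The article is a condensed account, mentions a separate full protocol, cites a source for this test that is not at hand, and names no mixed-model software.

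Part of this stands. It cannot be shown from the article that an invalid statistic would be computed. But REML is the only estimator named for these models and the comparison is described as one between those models. The point is therefore a stated combination that fails when followed, not a detail left out. If a refit is intended or happens silently, the text misdescribes the test.

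A reader might also infer that this trial's false-positive rate would be about 18%, 53% and 100% on its three primary outcomes. The document does not support that. Those rates belong to dummy coding, 51 complete cases per arm and assumed SDs. The intention-to-treat analysis is planned on all 132 randomized participants with imputation, and other codings make the test conservative. Nor is the distortion a matter of units alone, since coding matters as well.

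**Conclusion.** The point holds as a fault in the stated rule. As written, the treatment×time test compares REML fits with different fixed effects. Its statistic has no chi-square null distribution, and its p value depends on the outcome's units and on the coding of the factors. The unit dependence (4 ln c with three-level time) is algebraic and rests on no assumed value.

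The size of the error is conditional. With SDs of 4 to 18, correlation 0.5 and complete data, type I error ranges from about 1% to 100%, and it can fall on either side of the nominal 5%. The ML-based test stays near 5% in the same settings. No single rate within that range can be attributed to this trial, and the article does not establish that the restricted likelihoods would in fact be used.

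**What to change.** Add one sentence to Statistical Methods: the likelihood ratio test of treatment×time will be computed from maximum-likelihood fits of both the interactive and the additive model, and reported estimates and confidence intervals will come from the REML fit of the interactive model. An equally acceptable alternative is to drop the model comparison and test the interaction by an F test with Kenward-Roger or Satterthwaite degrees of freedom in the REML interactive model. The simulations give no reason to prefer one over the other.

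If the software to be used already refits by ML, the same sentence brings the text into line with what will be done.

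The cost is the sentence. Design, data collection and sample size are unaffected, and the article expects data analysis only in June 2029.
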